### Inclusion and Exclusion Criteria

All RAFCs located in regional and rural Queensland and New South Wales, Australia, are eligible for the study. Within each participating RACF, all permanent residents who are formally admitted for ongoing, long-term care, aged 65 years and older, or Indigenous Australians aged 55 years and older, who have at least 1 natural tooth, will be invited to participate.

Non-Indigenous Australians must be at least 65 years old to be eligible to enter a RACF. Aboriginal and Torres Strait Islander Australians can access RACF care from age 50, as they typically experience higher care needs at an earlier age.

Exclusion criteria include a known allergy to silver or fluoride and declining to undergo an oral examination or treatment. Participants who are noncompliant or who have not given assent for an oral examination will be excluded. A 3-attempt rule will be applied to obtain compliance and assent from the research team clinician before excluding participants.

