### Recruitment and Flow of the Study

Public and private aged care providers located in regional and rural Queensland and New South Wales, Australia, will be identified, approached, and provided with a Facility Participation Information and Consent Form prior to enrollment as study clusters. Once RACFs have consented, they will be randomly allocated in a 1:1 ratio to either the intervention or control arm using a computer-generated random sequence. Clusters assigned to the intervention arm will receive the AgF intervention at the first clinical visit, while those in the control arm will be offered the intervention after a 3-month delay. All individuals within a cluster will receive the same allocation condition. Study information materials, including leaflets and a short explanatory video, will be provided to participating RACFs for distribution within their facilities. Facility staff will identify and approach potentially eligible residents and coordinate scheduling with the study coordinator.

Upon arrival at the facility, the research team will meet with residents (and, where applicable, their Enduring Power of Attorney) to provide a detailed explanation of the study, confirm eligibility, and obtain written informed consent. Where there are any communication difficulties, RACF staff will be engaged to assist with facilitating communication. Once written informed consent has been obtained, the research team will administer a questionnaire, conduct an oral examination, and administer the AgF intervention in accordance with the study protocol.

For individuals requiring urgent dental care or identified as high risk of rapid oral health deterioration, regardless of their allocation, RACF staff will be advised by the research team clinicians, and referral will be made to their care facility to initiate appropriate action to access dental treatment. This does not exclude individuals from participating in the study.

At 3 months, the study coordinator will coordinate follow-up assessments with participating facilities. Ongoing consent will be confirmed with participants (and, where applicable, their Enduring Power of Attorney) prior to follow-up procedures.

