### Informed Consent

All residents who provide consent, or have consent provided on their behalf, and can provide assent will be invited to undertake baseline and follow-up surveys and a standardized oral epidemiological examination at the facility, followed by AgF treatment if needed.

Participation will be entirely voluntary. Participants will be assured that they are free to withdraw from the research at any time without providing an explanation.

Recruitment strategies will include internal newsletters distributed by industry partners, advertising flyers, prerecorded video information sessions, and posters displayed within facilities, all aligned with individual organizational protocols and governance requirements.

Participants will be made aware at multiple points (during recruitment and throughout the study) of the research aims, methods, procedures, and purpose, and will be informed of how their data are used, stored, and protected.

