### Intervention

AgF will be the intervention treatment used in this study. The first of the 2 bottles of the SDI Riva Star Aqua system (manufactured by Southern Dental Industries Ltd.), which contains 38% aqueous AgF, will be applied. This corresponds to step 1 of the manufacturer’s 2-step procedure. The decision to use only the first bottle is intended to simplify the application process and reduce treatment time. Using the first bottle of AgF ensures the evidence is relevant for generic AgF products, which is important for wider implementation of the findings.

At time 1 (the initial appointment, T1), all consented participants will undergo an oral examination to assess oral conditions and identify teeth requiring AgF treatment.

In an oral environment with a high risk of caries (eg, salivary gland hypofunction, acidic mouth pH), root surfaces and exposed dentin are at increased risk of dental caries developing. For participants assessed as being at high-risk of oral health issues developing, referral and discussion with the nurse coordinator at the facility will be undertaken as appropriate.

Participants in the intervention group will receive AgF during this first appointment. In contrast, participants in the control group will receive the same treatment at the 3-month follow-up appointment. AgF will be applied by the research team’s trained oral health professionals.

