#### Oral Health Status

Analyses will follow the intention-to-treat principle, whereby all participants will be analyzed according to their allocated cluster, regardless of adherence to the intervention. Generalized linear mixed-effects modeling will be used to quantify the treatment effect of AgF on oral health outcomes, including caries arrest, dental pain, and tooth sensitivity. If the extent of missing data exceeds acceptable thresholds, sensitivity analyses (eg, multiple imputation) will be conducted to assess the robustness of findings under different assumptions regarding missingness. Data from the intervention and control groups will be compared to estimate the treatment effect. These analyses will be undertaken at both the tooth or surface level and the participant level. Data from the standardized oral examination will provide caries status and tooth sensitivity at the tooth level, whereas pain and tooth sensitivity experiences at the participant level will be collected via visual analog scale and questionnaire on the presence of dental pain. Analyses will adjust for prespecified potential confounders at both resident and facility levels. Resident-level covariates will include age, sex, Aboriginal and Torres Strait Islander origin, baseline oral health measures, number of natural teeth, and relevant medical conditions where available. Facility-level factors, such as facility characteristics, will be considered where appropriate. These variables were selected a priori based on clinical relevance and existing literature. Baseline measures of the outcome variables, the time between T1 and T2, and other covariates relevant to each association of interest will be adjusted for in the analysis. The direction and magnitude of changes in the outcome measures, together with their respective CIs, will be estimated and reported.

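### Declining treatment excludes a resident, with no arm or time point given, although AgF is offered at T1 only in intervention facilities; the rule can select residents differently by arm and must be reconciled with the intention-to-treat statement.

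*Protocol article*

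**What the plan says.** Inclusion and Exclusion Criteria lists, besides silver or fluoride allergy, "declining to undergo an oral examination or treatment" as an exclusion. It adds: "Participants who are noncompliant or who have not given assent for an oral examination will be excluded". A three-attempt rule applied by the research clinician comes before exclusion. No arm or time point is attached to declining treatment.

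The surrounding sections fix the order of events:

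- **Allocation comes first.** Recruitment and Flow of the Study: "Once RACFs have consented, they will be randomly allocated in a 1:1 ratio to either the intervention or control arm". Facility staff then approach residents. The research team confirms eligibility and takes consent on site, before the questionnaire, the examination and AgF.
- **AgF is given at different times.** Intervention: "Participants in the intervention group will receive AgF during this first appointment", whereas "participants in the control group will receive the same treatment at the 3-month follow-up appointment". The T1 examination is also what identifies the teeth to be treated.
- **The clinical team is unblinded.** Blinding to Intervention says that no blinding of the clinical team will be attempted.
- **Consent is described once for everyone.** Informed Consent covers a "standardized oral epidemiological examination at the facility, followed by AgF treatment if needed", with no split by arm.
- **Exclusion is shown at enrollment.** Table 1 (Resident Participant Timeline) ticks the exclusion criteria in the Enrollment column, in one row for both arms.
- **The analysis is by intention to treat.** Oral Health Status: "all participants will be analyzed according to their allocated cluster, regardless of adherence to the intervention".

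**The concern.** At T1 only intervention residents can refuse an actual application. A control resident faces that decision three months later, at the visit where the outcomes are measured. A criterion that turns on refusing treatment therefore meets different circumstances in the two arms, after allocation, with a team that knows the allocation. This can happen in two ways:

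1. **At consent.** Agreeing to be treated today and agreeing to be treated in three months are different decisions. Even with one rule for all, the residents who pass it may differ by arm. This is recruitment bias, a known weakness of cluster trials that enrol after allocation.
2. **At the T1 visit.** If a refusal after the examination counts as declining treatment, the intervention arm keeps acceptors only and the control arm keeps acceptors and would-be refusers. That conflicts with analysis regardless of adherence.

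Residents who refuse, for example because of distress, dementia or worry about staining, may well differ in pain, sensitivity and caries. The difference would then enter the treatment comparison.

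**Working it through.** **The plan's detectable effects.** Inputs from Sample Size Calculation: 28 facilities (14 per arm), 25 completers each, ICC 0.15, alpha 0.05 (two-sided assumed), power 0.80 (stated for the categorical outcomes, assumed the same here).

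- Design effect = 1 + (25 − 1) × 0.15 = 4.6.
- Effective number per arm = 14 × 25 / 4.6 = 350 / 4.6 = 76.1.
- Standard error in SD units = √(2 / 76.1) = 0.162.
- Detectable effect = 0.454 with normal quantiles and 0.472 with t quantiles on 26 df. Power at 0.48 is 0.813 with the noncentral t. The stated 0.48 is reproduced.
- The stated 0.20 uses an individual autocorrelation of 0.5. Assuming also a cluster autocorrelation of 1 (not stated), the correlation of cluster means is (25 × 0.15 × 1 + 0.85 × 0.5) / 4.6 = 0.908. The detectable effect is then 0.191 (baseline as covariate) or 0.195 (change from baseline), in line with 0.20.

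Neither figure is challenged; they serve as yardsticks.

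**Bias if refusers leave one arm only.** Let q be the share who would refuse, the same in both arms, D the difference between refusers and acceptors in the untreated T2 outcome, in SD, and A the acceptor mean. With no treatment effect:

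- Intervention mean = A.
- Control mean = (1 − q)A + q(A + D) = A + qD.
- Bias = qD, with the sign of D, which is unknown.

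The documents give neither q nor D, so both are assumed:

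| q | D = 0.2 | D = 0.5 | D = 0.8 |
|---|---|---|---|
| 5% | 0.010 | 0.025 | 0.040 |
| 10% | 0.020 | 0.050 | 0.080 |
| 20% | 0.040 | 0.100 | 0.160 |

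For q = 10–20% and D = 0.5:

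- Against 0.20: 0.05 / 0.20 = 25% and 0.10 / 0.20 = 50%.
- Against 0.48: 0.05 / 0.48 = 10% and 0.10 / 0.48 = 21%.

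**Effect on type I error.** With the 0.162 standard error, biases of 0.05 and 0.10 SD raise the two-sided error from 0.05 to 0.061 and 0.095. With the standard error implied by 0.20, which is 0.20 / 2.80 = 0.071, they raise it to 0.108 and 0.288.

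**Baseline adjustment.** Oral Health Status adjusts for the baseline outcome. If refusers differ by the same D at baseline, a within-person correlation of 0.5 removes about half: 0.05–0.10 becomes roughly 0.025–0.05 SD. The 0.20 figure already uses the baseline, so on this assumption the share of it falls to 0.025 / 0.20 = 12.5% up to 0.05 / 0.20 = 25%.

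**If refusers are kept as allocated.** This bias does not arise. If refusers gain nothing from allocation, an effect of 0.48 becomes 0.48 × 0.9 = 0.432 at 10% refusal and 0.48 × 0.8 = 0.384 at 20%.

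**The case against.** A reader might infer that refusers are in fact removed from the intervention arm and that intention to treat is already lost. The documents do not support that:

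- Table 1 places exclusion at enrollment for both arms, and consent is sought before the examination and AgF.
- The consent description covers AgF for everyone, and Ethical Considerations says that staining is explained before application. On this reading a control resident unwilling to have AgF is excluded at the same step.
- Nothing says that an enrolled resident who refuses at T1 is dropped from follow-up or analysis. Oral Health Status, read alone, keeps that resident.
- An entry criterion applied before enrollment does not by itself breach intention to treat among those enrolled.
- The assent sentence concerns the examination, which both arms have at T1, so it shows no asymmetry.
- AgF goes only to clinically indicated teeth, so not every intervention resident can refuse it.

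These points stand, and they make the T1 route conditional. They do not close it. The criteria also exclude noncompliant participants after repeated attempts by the clinician, which is contact at the visit. Because the teeth to be treated are identified only at the T1 examination, a first refusal can come after T1 data exist. The consent route remains even if Table 1 is followed strictly.

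It is also fair to say that willingness to receive the study treatment, judged equally in both arms, is a legitimate entry criterion in a delayed-treatment design. Removing it is a choice and is not required.

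**Conclusion.** The concern holds as an ambiguity with a possible one-sided effect. The exclusion criterion does not say when or in which arm declining treatment counts. With allocation before consent, an unblinded team and AgF at T1 in one arm only, it can select residents differently by arm. Applied to a T1 refusal, it would exclude non-adherers from the intervention arm alone and contradict the intention-to-treat statement. That it is applied in this way is not documented.

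The size cannot be known from the documents. The 0.05–0.10 SD illustration rests on assumed refusal of 10–20%, an assumed difference of 0.5 SD, equal refusal in both arms and no baseline adjustment. It is material against the 0.20 detectable effect and modest against 0.48. The direction is unknown. The issue deserves correction because it decides who is in the main comparison of a trial that is already running.

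**What to change.** Reconcile Inclusion and Exclusion Criteria with Oral Health Status.

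1. Either delete treatment from the declining criterion, or state that willingness to receive AgF is judged once, at consent, before the T1 examination and with identical wording in both arms.
2. In either case, define the analysis population in both arms as residents with consent or assent and a completed T1 examination.
3. Keep residents who later decline AgF in follow-up, unless they withdraw consent, and in the intention-to-treat analysis as allocated. Their freedom to decline is unchanged.
4. For facilities already visited (25 enrolled and about 20 through follow-up as of February 2026, per Results), establish whether any examined resident was excluded for refusing AgF. Include those whose data may be used.
5. Report refusals by arm and time point. An analysis of acceptors can be supportive only.

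The protocol says that its analysis plan will be finalized before data are available, so the population can be fixed there. The cost is wording, a check of visit records and slight dilution of the estimated effect. The first option in step 1 also admits residents known in advance to be unwilling, which the second avoids.

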### Informed Consent

All residents who provide consent, or have consent provided on their behalf, and can provide assent will be invited to undertake baseline and follow-up surveys and a standardized oral epidemiological examination at the facility, followed by AgF treatment if needed.

Participation will be entirely voluntary. Participants will be assured that they are free to withdraw from the research at any time without providing an explanation.

Recruitment strategies will include internal newsletters distributed by industry partners, advertising flyers, prerecorded video information sessions, and posters displayed within facilities, all aligned with individual organizational protocols and governance requirements.

Participants will be made aware at multiple points (during recruitment and throughout the study) of the research aims, methods, procedures, and purpose, and will be informed of how their data are used, stored, and protected.

### Sample Size Calculation

The primary outcome of AgF effects on dentin hypersensitivity was used for the sample size calculation. Based on estimates presented by Chan et al [23] and Castillo et al [32] assessing AgF effects on dentin hypersensitivity using a visual analog score, a mean difference of 2.9 units with a SD of 2.6 indicates that a total of 8 clusters (4 per arm) is required to achieve statistical power greater than .80 (*β*>.80), assuming a significance level of .05 (*α*=.05) and 25 participants per cluster. To account for potential attrition, we plan to increase the cluster size by at least 50%, resulting in 40 participants per cluster at baseline. This would yield 160 participants in each group, for a total of 320 participants.

Given the absence of known adverse health effects from AgF and the likelihood that participants will benefit from access to an otherwise unavailable health intervention, we propose overenrolling sites. Specifically, the aim is to recruit 28 clusters (14 per arm), with up to 40 participants per site. This will improve the precision of our estimates of efficacy. This oversampling is planned to account for potential within-facility clustering in residential aged care settings.

Assuming 25 participants per site complete both baseline and follow-up assessments and using a conservative intracluster correlation coefficient (ICC) of 0.15, this sample size will allow detection of an effect size of approximately 0.48 (Cohen *d*) [33]. For categorical outcomes, this sample would be powered at 0.80 to detect a 23% difference between groups, assuming a 50% control group proportion.

Using more precise parameters for this study design, 28 clusters with 25 individuals providing complete data and an individual autocorrelation of 0.5, the minimum detectable effect size decreases to 0.20 (mean difference divided by SD). For categorical outcomes, the same design would be powered at 0.80 to detect a 10% absolute difference, again assuming a control proportion of 0.5.

All sample size and power calculations were informed by Hemming et al [34] and conducted using the Shiny CRT Calculator: Power and Sample Size for Cluster Randomized Trials.

### Intervention

AgF will be the intervention treatment used in this study. The first of the 2 bottles of the SDI Riva Star Aqua system (manufactured by Southern Dental Industries Ltd.), which contains 38% aqueous AgF, will be applied. This corresponds to step 1 of the manufacturer’s 2-step procedure. The decision to use only the first bottle is intended to simplify the application process and reduce treatment time. Using the first bottle of AgF ensures the evidence is relevant for generic AgF products, which is important for wider implementation of the findings.

At time 1 (the initial appointment, T1), all consented participants will undergo an oral examination to assess oral conditions and identify teeth requiring AgF treatment.

In an oral environment with a high risk of caries (eg, salivary gland hypofunction, acidic mouth pH), root surfaces and exposed dentin are at increased risk of dental caries developing. For participants assessed as being at high-risk of oral health issues developing, referral and discussion with the nurse coordinator at the facility will be undertaken as appropriate.

Participants in the intervention group will receive AgF during this first appointment. In contrast, participants in the control group will receive the same treatment at the 3-month follow-up appointment. AgF will be applied by the research team’s trained oral health professionals.

### Site Randomization

RACFs of varying socioeconomic status are being recruited in this trial. These organizations will be independently assigned through randomized blocks of even numbers of RACFs to maintain balance throughout the trial period between the control and intervention arms. If any participating sites withdraw, replacement sites will be matched with similar parameters of postcode and number of beds.

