### Blinding to Intervention

In accordance with the CONSORT (Consolidated Standards of Reporting Trials) 2025 guidelines for cluster randomized trials [35], blinding will be implemented where feasible to minimize bias. As the AgF application leaves a distinct black stain on carious lesions, this may inadvertently reveal allocation status to participants, RACF staff, and treating clinicians. Therefore, no attempt will be made to blind the clinical team. To mitigate bias in outcome assessment, both site identity and treatment allocation will be blinded during data analysis. A detailed statistical analysis plan will be finalized, and analysis syntax prepared, prior to data availability. Data analysts will receive deidentified datasets with anonymized group labels (eg, Group A and Group B), and the allocation decoding key will be securely retained by the project lead until primary analyses are completed.

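### Withdrawn facilities are replaced by sites matched on postcode and bed count, with no statement of how the replacement's arm is assigned

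*Protocol article*

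**What the plan says.** Three sections of the protocol article bear on this.

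- **Recruitment and Flow of the Study** sets the general rule: "Once RACFs have consented, they will be randomly allocated in a 1:1 ratio to either the intervention or control arm". It makes no exception for facilities that join as replacements.
- **Site Randomization** describes the mechanism: "These organizations will be independently assigned through randomized blocks of even numbers of RACFs to maintain balance throughout the trial period". The section then adds the replacement rule: "If any participating sites withdraw, replacement sites will be matched with similar parameters of postcode and number of beds". It does not state the arm a replacement enters, who selects it, whether the rule applies before or after residents are enrolled, or what becomes of the withdrawn site's data.
- **Oral Health Status**, in the analytical plan, commits to intention to treat: "all participants will be analyzed according to their allocated cluster, regardless of adherence to the intervention".

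Two further statements matter. Under Blinding to Intervention, "no attempt will be made to blind the clinical team". Under Sample Size Calculation, "the aim is to recruit 28 clusters (14 per arm), with up to 40 participants per site", although by the protocol's own calculation "a total of 8 clusters (4 per arm) is required to achieve statistical power greater than .80".

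**The concern.** Matching a new facility to a departed one serves little purpose if the new one is then randomised afresh, because it may land in the other arm. Postcode and bed count are not named anywhere as stratification or pairing factors, so matching on them does not serve the randomisation scheme as described. The rule is most coherent if the replacement fills the vacated place and inherits its arm.

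On that reading the replacement's arm is fixed before the site is chosen. Whoever selects the facility, and the facility when it agrees, may know which arm is on offer. Control facilities wait three months for treatment, so both withdrawal and willingness to step in could depend on the arm. Facility staff also identify and approach residents after allocation, which gives a further route for selection. Similarity on two facility characteristics does not replace random assignment.

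The second risk concerns the analysis. If replacement means that the withdrawn cluster is swapped out of the data set, the comparison is no longer by allocated cluster.

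**Working it through.** **Inputs** (all from Sample Size Calculation unless marked): 14 facilities per arm; 25 completers per facility; ICC 0.15; power 0.80; alpha 0.05, taken as two-sided (assumed, sidedness is not stated); stated detectable effects of about 0.48 (first calculation) and 0.20 (with an individual autocorrelation of 0.5).

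**1. Reproducing the plan's figure.** Design effect = 1 + (25 − 1) × 0.15 = 4.6. Detectable effect = (critical value + power quantile) × √(2 × 4.6 / (14 × 25)), and the square root is 0.162.
- Normal quantiles: (1.960 + 0.842) × 0.162 = 0.454.
- t quantiles, 26 df: (2.056 + 0.856) × 0.162 = 0.472.

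The stated value of about 0.48 is reproduced closely enough.

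**2. Is replacement needed for power?** Same formula with t quantiles:

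| Facilities per arm | Detectable effect |
|---|---|
| 14 v 14 | 0.472 |
| 13 v 13 | 0.491 |
| 12 v 12 | 0.513 |

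Even at the protocol's minimum of 4 v 4, with its difference of 2.9 and SD of 2.6 and an ICC of 0.15, power is 0.863 with t (6 df) and 0.957 with the normal approximation.

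**3. What could substitution do to the comparison?** The scenario is assumed: three substitutions, all in one arm, each one facility SD away from the site it replaces and in the same direction.
- Facility SD = √0.15 = 0.387 outcome SD.
- Shift per substitution = 0.387 / 14 = 0.028 SD.
- Three substitutions = 0.083 SD.
- Against the detectable effect on the same unadjusted basis: 0.083 / 0.48 = 17%.

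**4. What survives baseline adjustment?** Suppose facility effects are fully stable between baseline and follow-up, and individual autocorrelation is 0.5.
- Variance of a facility mean = 0.15 + 0.85/25 = 0.184.
- Covariance of its baseline and follow-up means = 0.15 + 0.5 × 0.85/25 = 0.167.
- Correlation = 0.167 / 0.184 = 0.91.
- Remaining shift = 0.083 × (1 − 0.167/0.184) = 0.008 SD.

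This stability assumption is also the one that reproduces the protocol's 0.20. A change-score analysis has variance 2 × (0.184 − 0.167) = 0.034 per facility mean, so the detectable effect is 2.802 × √(2 × 0.034/14) = 0.195 with normal quantiles and 2.912 × √(2 × 0.034/14) = 0.203 with t. If facility effects are less stable, adjustment removes less of the shift and the 0.20 no longer holds.

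**The case against.** The strongest reply is that the article never says replacements bypass randomisation. Read literally, the recruitment section randomises every consenting facility, and matching may describe only which kind of facility is approached, so as to keep the mix stable. That stands: inheritance of the arm is the more natural reading but remains an inference.

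A reader might also infer that the plan already contradicts intention to treat. The documents do not support this. No section says a withdrawn facility's residents are removed, and a site that leaves before enrolling anyone has no resident data to keep. The conflict arises only if data are dropped.

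It is tempting to set the 0.083 SD shift against the 0.20 detectable effect and report 41%. That mixes two bases: the shift is unadjusted, while 0.20 relies on baseline measurements. On the assumption that yields 0.20, about 0.008 SD remains, or 0.008 / 0.20 = 4%. It is likewise too strong to say that no model term could reduce the bias. The planned adjustment for baseline outcomes, number of teeth and medical conditions should absorb much of a stable difference, though not differences in unmeasured features or in response to treatment.

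The scenario itself is unfavourable by construction. The Results section reports 25 facilities enrolled by February 2026, with baseline and follow-up done in about 20, and mentions no withdrawal or replacement.

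Finally, a condensed article may leave operational detail to the full protocol or the SAP. That excuses silence, but here the article states a rule, and the rule it states is the weak point. An SAP can define how withdrawn clusters are analysed; it cannot randomise a site that has already been placed.

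**Conclusion.** The concern holds in conditional form. The protocol sets a matched-replacement rule without saying how the replacement's arm is assigned. If the arm is inherited, a non-randomised facility enters an open trial, contrary to the recruitment section. If withdrawn clusters are also dropped, the analysis departs from intention to treat.

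The likely size is modest: about 17% of the 0.48 detectable effect under an adverse assumed scenario before adjustment, and close to nothing after adjustment if facility differences are stable over the three months. The number of substitutions and the one-SD difference are assumptions with no basis in the documents. Against this, the rule buys almost no precision. It should be corrected because the remedy is cheap and recruitment was still open at the last report, not because the trial's result is shown to be biased.

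**What to change.** Replace the matching sentence with a rule on these lines: any added facility takes the next unused allocation in the concealed block sequence, whichever arm that is; a withdrawn facility stays in its allocated arm, and all data collected from it are analysed there. This brings Site Randomization into line with the recruitment section and the intention-to-treat commitment.

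Report withdrawals and replacements by arm. If any replacement has already been placed without randomisation, flag it and present the analysis with and without such sites.

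The cost is a change of wording and, if needed, one further analysis. Arm sizes may differ by a site or two. With normal quantiles, the detectable effect is 0.454 at 14 v 14, 0.463 at 13 v 14 and 0.473 at 12 v 14, so the loss is small.
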